#### Safety Outcome Measurement

The safety of this study will be assessed based on vital signs, physical examinations, and disease occurrence status. There is a risk of injury because of falls; therefore, a fall-prevention device (All-In-One Walking Trainer) will be used if necessary. The disease occurrence status in this study is defined as worsening of undesirable or unintended diseases, disorders, signs, symptoms, or medical conditions occurring in the study participants. If a disease occurrence status is detected, the investigator will immediately take appropriate measures and file a consistent medical record and case report. If the disease occurrence status is attributed to a mechanical problem with the HAL system, the investigator will check the records for errors in the history of the device’s operation and confirm the test equipment failure.

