## Methods and Analysis

### Objective

The purpose of this RCT is to evaluate the efficacy and safety of gait treatment using HAL versus CGT among hemiplegic patients with acute stroke and collect outcome data such as improvement of independent walking, gait speed, and endurance.

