### Criteria for Discontinuation (Discontinuation of Protocol Treatment)

1)When a patient requests to decline participation in the study or withdraws consent.2)If it turns out that a patient is not satisfied with his or her eligibility after registration.3)When it is judged that it is not preferable to continue using the test equipment due to worsening of the underlying disease.4)When it is difficult to continue the study due to exacerbation of complications.5)When it is difficult to continue the study due to illness or other reasons.6)When the entire study is discontinued.7)When the doctor deems it inappropriate to continue the study for other reasons.

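### The safety event is defined as a worsening only, so new-onset events fall outside the wording although the same section shows they are meant

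*Protocol article*

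**What the plan says.** The Objective section makes safety part of the trial's aim: "The purpose of this RCT is to evaluate the efficacy and safety of gait treatment using HAL versus CGT".

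Safety Outcome Measurement rests the safety assessment on three things: vital signs, physical examinations and a term it calls disease occurrence status. It defines the third: "The disease occurrence status in this study is defined as worsening of undesirable or unintended diseases, disorders, signs, symptoms, or medical conditions". The sentence ends by placing these in the study participants.

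The same section attaches a duty to that term: "If a disease occurrence status is detected, the investigator will immediately take appropriate measures and file a consistent medical record and case report". It names one hazard, "There is a risk of injury because of falls", and adds a rule on checking device records that begins "If the disease occurrence status is attributed to a mechanical problem with the HAL system".

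The Criteria for Discontinuation use *worsening* once more, where it is "not preferable to continue using the test equipment due to worsening of the underlying disease". A separate criterion there covers the case where it is "difficult to continue the study due to illness or other reasons".

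**The concern.** A safety event is normally understood to include both a condition that appears for the first time and an existing condition that gets worse. This definition states only the second. An investigator who follows it to the letter would treat a patient's first injury from a fall, or a first skin lesion under an electrode, as outside the defined term, and so outside the duty to act immediately and file a case report.

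Two features make the wording worth correcting. Safety is half of the stated purpose, and this is the only definition of a safety event in the article. Also, under Allocation and Blinding only the FAC score is assessed blind, so the definition will be applied by staff who may know the allocation. A term that has to be reinterpreted in use leaves them more discretion than it should.

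**Working it through.** The protocol gives no figure on this point, so the check is a reading of the text.

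**1. Where the term is used.** *Disease occurrence status* appears 4 times, all in Safety Outcome Measurement: once in the list of safety bases, once in the definition, once in the reporting duty and once in the device-fault rule. There is one definition, and no other section gives a broader one.

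**2. What the definition requires.** The fuller run is "The disease occurrence status in this study is defined as worsening of undesirable or unintended diseases, disorders, signs, symptoms, or medical conditions occurring in the" participants. The head noun is *worsening*. There are two ways to attach *occurring*:

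- To *worsening*: a worsening that occurs in a participant.
- To the listed conditions: a worsening of conditions that occur in a participant.

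Both readings require a worsening. Five kinds of condition are listed (diseases, disorders, signs, symptoms, medical conditions). All 5 stand under *worsening*, and first onset is stated for 0 of 5.

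**3. What the rest of the section implies.**

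| Text in the same section | Kind of event it implies | Covered by the literal definition? |
|---|---|---|
| The term itself (*occurrence*) | Onset | No |
| Injury from falls as the named risk | Naturally a new injury | No, unless it aggravates an existing condition |
| Event attributed to a HAL mechanical problem | Ordinarily a new injury | No, unless it aggravates an existing condition |

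A first skin lesion at an electrode site is a further foreseeable example, because the HAL System and Treatment section places electrodes on the skin. The safety section does not name it. These examples illustrate the gap; they do not measure it.

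**4. How the article uses the word elsewhere.** *Worsening* appears 2 times in all. The other use, in the Criteria for Discontinuation, concerns a disease already present. Illness is a separate criterion there. A new illness could therefore end protocol treatment and still not meet the safety definition as worded.

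**5. Effect on the trial's numbers.** The sample size (34, target 40) rests on the FAC difference and its SD, and the primary analysis is of FAC change. Neither uses the safety definition, so neither changes.

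**The case against.** The strongest reply is that this is a slip of language in a condensed article and that the section corrects itself. The term says *occurrence*, the sentence speaks of undesirable or unintended conditions occurring in participants, and the device rule treats device-caused events as falling under the term. A definition is read together with the rules that use it, and few investigators would withhold a report of a first fall injury. Safety capture also does not rest on this term alone: vital signs and physical examinations are listed beside it, and the Treatments section has staff watch for pain and fatigue during the programme. The stopping criteria are not safety definitions, and nothing says that an illness which ends treatment goes unrecorded. Finally, the full protocol approved by the review board is not shown and may be worded correctly.

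Much of this stands. The intended meaning can probably be recovered, the stopping criteria are only supporting evidence, and the article gives no ground for saying that events will be missed.

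It does not remove the point. The device rule applies only once a disease occurrence status exists; it shows what was meant without widening what the definition says. Vital signs and physical examinations do not carry the reporting duty, which is tied to the defined term. Nor is this a detail left to a fuller document: the article states a definition, and the definition as stated is too narrow.

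**Conclusion.** The concern holds, at minor severity. The article's only definition of a safety event covers worsening for all five kinds of condition and first onset for none, which contradicts the evident intent of the section it stands in. The fault is in the wording; nothing suggests that new-onset events were deliberately excluded.

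The practical effect depends on how literally staff read the sentence, and the number of events affected cannot be derived from the document. The conclusion rests on the published article; whether the full protocol carries the same wording is unknown.

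**What to change.** Replace the definition so that disease occurrence status means *the occurrence or worsening of any undesirable or unintended disease, disorder, sign, symptom or medical condition in a study participant*. It is worth adding that this applies identically in both arms: the present text makes no distinction between them, and the staff applying the definition are not stated to be blinded.

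If the full protocol already reads this way, only the article needs correcting. The cost is one phrase in one sentence. If staff already read the term as intended, the recording burden does not change; if they read it literally, there will be slightly more events to record.

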### Participant Timeline (Figure 3)

This study will include three phases: (1) pre-observation phase (patient enrollment, baseline assessment, and randomization); (2) treatment phase [the patients will undergo a total of nine sessions, twice or thrice per week over 3−4 weeks; the HAL and control groups will perform gait treatment with HAL and CGT, i.e., walking aids and gait orthoses, respectively, as follows: initial treatment phase evaluation, 1st interim evaluation (before the 4th intervention), and 2nd interim evaluation (before the 7th intervention)]; and, finally (3) post-treatment evaluation phase (after the 9th intervention). Subsequently, a 6-month post-treatment evaluation (follow-up assessment) will be conducted to assess body functions, walking ability, ADL, and QOL in the post-observation phase.

**FIGURE 3 F3:**
[figure not shown]
Participant timeline of the study. This single-center, randomized, parallel-group, controlled trial will include three phases: (1) pre-observation phase (patient enrollment, baseline assessment, and randomization); (2) treatment phase [patients will undergo a total of nine sessions, twice or thrice per week over 3–4 weeks; the HAL and control groups will undergo gait treatment with HAL and CGT, i.e., walking aids and gait orthoses, respectively, as follows: initial treatment phase evaluation, 1st interim evaluation (before the 4th intervention), and 2nd interim evaluation (before the 7th intervention)]; and, finally (3) post-treatment evaluation phase (after the 9th intervention). Subsequently, a 6-month post-treatment evaluation (follow-up assessment) will be conducted to evaluate body functions, walking ability, ADL, and QOL in the post-observation phase. HAL, Hybrid Assistive Limb; CGT, conventional gait training; ADL, activities of daily living; QOL, quality of life.

### Criteria for Discontinuation (Discontinuation of Protocol Treatment)

1)When a patient requests to decline participation in the study or withdraws consent.2)If it turns out that a patient is not satisfied with his or her eligibility after registration.3)When it is judged that it is not preferable to continue using the test equipment due to worsening of the underlying disease.4)When it is difficult to continue the study due to exacerbation of complications.5)When it is difficult to continue the study due to illness or other reasons.6)When the entire study is discontinued.7)When the doctor deems it inappropriate to continue the study for other reasons.

### Data Management

The research data will be saved in a personal computer of the Center for Innovated Medicine and Engineering at the University of Tsukuba Hospital, and a back-up copy will be stored in an external hard disk. Computer access will require a password to prevent third-party viewing. The researcher will be responsible for data storage endeavors aimed at ensuring that the research documents will not be lost, discarded, or stolen over 10 years.

### Data Monitoring

The investigator will appoint a person who is not directly involved in the clinical trial to act as the monitor, who will be responsible for regularly monitoring data quality, written informed consent documents, protocol compliance, and overall clinical trial progress during the study, as well as reporting these items to the investigator in writing. The monitoring work will be conducted by the staff of the University of Tsukuba, Tsukuba Clinical Research & Development Organization.

### Sample Size

We calculated the sample size of this study based on our exploratory study (Watanabe et al., 2020), the results of which led us to estimate that the mean difference of the change in the intervention group at the end of the FAC was 0.82 and the combined SD was 0.63. However, the 50% lower confidence limit of the mean difference, 0.63, was used conservatively in consideration of the small sample size and design difference of the exploratory study. The minimum sample size necessary for the power of the primary analysis to exceed 0.8 was estimated as 34 in two groups. Considering information loss because of missingness, the target number of cases was set to 40 in two groups.

### Statistical Analysis

The target population in this analysis will be all participants who have undergone at least one intervention during the study period, including the pre-observation period. The significance level will be 5% on both sides, and the confidence level will be 95%. We will test differences in the baseline variables between the HAL and CGT groups using the Fisher exact test for categorical data and Mann–Whitney *U* test for continuous data. The primary analysis will consist of mixed effect models for repeated measures (Mallinckrodt et al., 2001) to reduce bias due to dropouts, in which changes in FAC at the 4th, 7th, and 9th interventions and at 6 months from the baseline will be included as the outcome variable. Whereas, group, time point, and the group × time point interaction will be included as the fixed effects. Using this model, a *t*-test will be performed on the difference in the adjusted mean between the intervention groups at the time of the end-of-term evaluation. In this analysis, we do not plan to conduct a preliminary test for the diagnosis of normality because of robustness of the statistical model with the normal distribution (Heeren and D’Agostino, 1987; Maruo et al., 2017) and the inflation of type I error due to the preliminary tests (Shuster, 2005, 2009). For other analyses, summary statistics will be calculated for the patient background factors. The summary statistics refer to the number of cases, mean value, standard deviation, minimum value, median value, and maximum value for continuous variables and the number of cases and their ratios for categorical variables. For the primary and secondary endpoints, the summary statistics will be calculated for each evaluation time point. For the primary analysis, we will estimate the differences between the groups at different time points. An analysis similar to the primary analysis will be performed for the secondary continuous outcome measures. All statistical analyses will be conducted using IBM SPSS version 26.0 (IBM Corp., Armonk, NY, United States) and SAS version 9.4 (SAS Institute Inc., Cary, NC, United States).

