### Allocation and Blinding

Enrolled patients will be randomly assigned to either the HAL group or the CGT (control) group at a 1:1 allocation ratio via the minimization method using the Electronic Data Capture (EDC) clinical research support system. The Alliance Clinical Research Support System will be used as the EDC system, and random allocation factors for age (older than 65 years or younger than 65 years) and FAC (scores of 0–1 or ≧2) will be set at baseline. Regarding the blinding technique, only the primary outcome measure (FAC score) will be blinded using third-party assessment. Specifically, video-based FAC assessment will be performed by a third-party physical therapist who will not be involved in patient treatment or assessment and who will be blinded to the allocation. These measures will be implemented to reduce biases, improve the quality of the research, and ensure comparability. It will not be possible to use the blinding technique among the participants (patients) and the treatment providers (physical therapists) as they will inevitably know the allocation group. Therefore, it will be difficult to use the placebo technique in this study.

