The present study has several limitations. First, this study is an RCT comparing groups using the minimization method; however, because of the small sample size, parameters other than the allocation factors (FAC and age at baseline) may be imbalanced between the two groups. Second, this study is not a multicenter trial but a single–institution trial, and the results are unlikely to be generalized. Third, it is not possible to blind the participants and the treatment providers (physical therapists); therefore, in this study, it is not possible to perform sham interventions or set up a third-party physical therapist.

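### Baseline significance tests are planned in a randomised trial of 40, while the stated primary model leaves out baseline FAC and age, the two minimisation factors

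*Protocol article*

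**What the plan says.** All references are to the protocol article.

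- **Statistical Analysis, baseline:** "We will test differences in the baseline variables between the HAL and CGT groups using the Fisher exact test for categorical data"; continuous variables get a Mann–Whitney test. The level given for the analysis is "The significance level will be 5% on both sides, and the confidence level will be 95" per cent, and no separate level is set for the baseline tests. The number of variables to be tested is not given. Summary statistics for background factors are planned as well.
- **Statistical Analysis, primary model:** a repeated-measures mixed model for change in FAC, in which "group, time point, and the group × time point interaction will be included as the fixed effects". No baseline covariate is named.
- **Allocation and Blinding:** assignment is "at a 1:1 allocation ratio via the minimization method", with "random allocation factors for age (older than 65 years or younger than 65 years) and FAC" (0–1 versus 2 or more).
- **Sample Size:** "The minimum sample size necessary for the power of the primary analysis to exceed 0.8 was estimated as 34 in two groups", and "the target number of cases was set to 40 in two groups".
- **Discussion, limitations:** because the sample is small, "parameters other than the allocation factors (FAC and age at baseline) may be imbalanced between the two groups".

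**The concern.** Two choices sit badly together. The plan tests baseline differences between arms that an allocation algorithm has formed, so the tests mostly ask whether chance produced what chance is known to have produced. For FAC and age the algorithm forces balance, so ordinary p-values for those two are also miscalibrated, on the conservative side.

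Meanwhile the tool that does deal with baseline differences, covariate adjustment fixed in advance, is absent from the stated model even for the two factors judged important enough to steer allocation.

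The tests put interpretation at stake. A non-significant result may be taken as evidence of comparability that 40 patients cannot supply, and a significant one may be taken as a flaw in the randomisation. The model puts the precision of the primary comparison at stake, together with its protection against residual imbalance in FAC and age.

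**Working it through.** **1. The plan's own figure.** Inputs from Sample Size: difference 0.63, SD 0.63, so the standardised effect is 0.63/0.63 = 1.0, at two-sided 5%. A two-sample t-test has power 0.781 with 16 per arm and 0.807 with 17 per arm. The minimum is 2 × 17 = 34, as stated. Going from 34 to 40 corresponds to 15% loss (34/0.85 = 40). The sample size reproduces and is not in question.

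**2. Chance of at least one significant baseline test.** The article lists FAC and 14 secondary measures, which makes 15, plus unspecified background factors. The count is an assumption, taken as 10 to 20.

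For k independent tests of true 5% size the chance is 1 − 0.95^k:
- k = 10: 0.40
- k = 15: 0.54
- k = 20: 0.64

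Many of these measures are related (gait speed, 6-minute distance, step length and cadence; Barthel Index, FIM and modified Rankin Scale). Simulating 4,000 trials of 20 versus 20, with equally correlated normal variables and Mann–Whitney tests, gives:

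| k | ρ = 0.3 | ρ = 0.5 | ρ = 0.7 |
|---|---|---|---|
| 10 | 0.36 | 0.30 | 0.22 |
| 15 | 0.47 | 0.37 | 0.27 |
| 20 | 0.55 | 0.44 | 0.31 |

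Fisher's test lowers these further, because its actual size at 20 versus 20 is only 0.012 to 0.025 for prevalences of 10% to 50%.

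**3. What a non-significant test can hide.** The smallest significant observed difference, by a t approximation, is t(0.975, 38) × √(2/20) = 2.024 × 0.316 = 0.64 SD. An observed 0.5 SD gives t = 0.5/0.316 = 1.58, p about 0.12. For any one variable not balanced by design, a difference of 0.5 SD or more in either direction arises by chance in about 11% of randomisations. For a binary factor, 13/20 versus 7/20 gives p = 0.11, and 14/20 versus 6/20 gives p = 0.026.

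**4. What omitting FAC and age costs.** With SD 0.63 and 20 per arm, the unadjusted standard error at one time point is 0.63 × √(2/20) = 0.199. If baseline FAC and age together have multiple correlation r with FAC change, adjustment multiplies it by about √(1 − r²), ignoring the small loss of degrees of freedom. The documents give no r, so a range is shown:

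| r (assumed) | √(1 − r²) | adjusted standard error |
|---|---|---|
| 0.3 | 0.954 | 0.190 |
| 0.5 | 0.866 | 0.173 |
| 0.7 | 0.714 | 0.142 |

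Minimisation balances only the categories. Since entry requires FAC 0–2, the lower FAC category mixes scores 0 and 1, and the age factor is a single cut at 65. Differences inside those categories remain, and the stated model does not correct them.

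**The case against.** **No decision depends on the baseline tests.** This stands. Nothing in the article lets a baseline p-value choose covariates, alter the primary model or discount the result. The same section declines preliminary normality tests because they inflate type I error. Deleting the baseline tests would by itself change no estimate.

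**The null hypothesis is not guaranteed.** This stands in part. The analysis set requires at least one intervention in an unblinded trial, and the HAL-fit criterion is worded for the HAL group only, so losses before the first session could differ by arm. The article does not give the tests that purpose, however, and they would detect such loss poorly. Reporting exclusions by arm addresses it directly.

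**An article condenses the full plan.** The full protocol or SAP may name covariates. The point rests on what the article does state: it lists the fixed effects, and baseline FAC and age are not among them.

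A reader might also draw stronger conclusions that the documents do not support:

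- *That the tests raise a false alarm about half the time.* This needs about 13 to 15 independent tests of true 5% size. Neither the number nor the independence is stated, and the figure would be the chance of at least one significant result, not a rate per test.
- *That the tests find a 0.5 SD imbalance only 32% of the time.* That is Mann–Whitney power against a true population shift, which randomisation rules out. The relevant quantity is the observed difference in step 3.
- *That the tests let a distortion of the result through.* A 0.5 SD imbalance in a factor correlated 0.3 to 0.5 with FAC change would shift the unadjusted difference by 0.5 × 0.3 × 0.63 = 0.09 to 0.5 × 0.5 × 0.63 = 0.16 FAC points. Those correlations are assumed, and the shift comes from the unadjusted model, so removing the tests leaves it unchanged.

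**Conclusion.** The concern holds as a minor point with a free remedy. The baseline tests are uninformative in both directions: a chance of roughly a quarter to a half of at least one spurious flag for about 15 correlated variables (22% to 64% over the whole range considered), and no flag for observed differences below about 0.64 SD. Their harm is confined to interpretation.

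The part that affects the primary result is the model. Minimising on FAC and age and then omitting them leaves the standard error too large, by an amount that depends on how well they predict FAC change. Under the illustrative r of 0.3 to 0.5, adjustment would reduce it by about 5% to 13%; if they predict nothing, there is no gain. The omission also leaves within-category imbalance in these two factors uncorrected.

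The size rests on an assumed number of baseline variables, assumed correlations among them and an assumed r. That the tests are planned and that the listed fixed effects exclude FAC and age rests on stated text alone.

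**What to change.** 1. In Statistical Analysis, add baseline FAC and age to the fixed effects of the primary mixed model, state their form (score or category, years or cut at 65), and say that they enter whatever imbalance is observed.
2. Delete the sentence on Fisher and Mann–Whitney testing of baseline variables.
3. Keep the planned summary statistics for background factors and show them by arm. Standardised differences may be added.

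Adjusting for FAC and age will not generally remove imbalance in other factors. That remains the limitation already conceded in the Discussion, and the text should not suggest otherwise.

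Cost: a wording change. Both covariates are already collected for allocation, no patient or visit is added, and the sample sizes of 34 and 40 are unchanged.

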The single-leg version of the HAL is a new wearable cyborg designed to be used by patients with hemiplegia (Kawamoto et al., 2009; Watanabe et al., 2014, 2017). In addition, many clinical studies have been conducted on the application of HAL to both legs in patients with stroke (Sczesny-Kaiser et al., 2019; Yokota et al., 2019; Taki et al., 2020). In Japan, a doctor-initiated clinical trial of the single-leg version of HAL as a medical device application (HAL-TS01) in patients with stroke-induced hemiplegia in the late recovery phase is currently underway (Tsurushima et al., 2019). To the best of our knowledge, one randomized controlled trial (RCT) has compared HAL with conventional therapies regarding patient outcomes after subacute stroke (within 5 weeks after stroke onset) (Wall et al., 2020). In their RCT, Wall et al. (2020) reported no between-group difference in any outcome, including the functional ambulation category (FAC) score after intervention or at 6 months after stroke, despite the extra resources required for the HAL training. In addition, younger age was determined as the only factor that enhances independent walking. However, the authors indicated that there was room for consideration of HAL treatment methods (treadmill or overground gait training) based on indications and other factors.

The results of our previous non-randomized clinical trial suggested that the HAL treatment group showed a significant improvement in FAC after nine sessions compared with the conventional treatment group (Watanabe et al., 2020). Furthermore, examination of changes in FAC on a weekly basis revealed a significant group × time point interaction in FAC of the HAL treatment group, suggesting that independent walking may be improved at an early stage [unpublished data]. However, because the study did not have an RCT design, it was thought that there were many biases and variations, as well as a problem in ensuring comparability. Therefore, we planned an RCT to compare the efficacy and safety of HAL treatment with those of conventional gait training (CGT) in patients with hemiplegic acute stroke.

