A previous RCT reported no differences between the HAL and control groups for any outcome, including the FAC score after the intervention or at 6 months after stroke, despite the extra resources required for the HAL training (Wall et al., 2020). Among the patients with an FAC score of 0–1 who participated in the previous RCT, approximately 70% had an FAC of 0 and severe gait disturbance. The average time from the onset of stroke was approximately 5 weeks, which corresponded to the subacute stage (within 5 weeks after stroke onset), and the patients were relatively young (16–67 years). The intervention was conducted 4 times per week, 16 times in total for 4 weeks, and HAL treatment was performed on a treadmill (Wall et al., 2020). In contrast, the present RCT will target patients with an FAC score of 0–2 within 3 weeks of stroke onset. The inclusion criteria for this study include patients who can undergo gait training using a mobile suspension system (All-In-One Walking Trainer) and patients who can walk even with an FAC score of 0. In addition, age and FAC scores will be used as allocation factors to equalize the age and walking ability between the two groups. At present, it is not possible to discuss whether a treadmill or overground gait training is a good intervention method for HAL treatment, but we have selected overground gait training, which is similar to normal walking. In addition, a recent Cochrane report described that the evidence showing the effectiveness of treadmill training for walking after stroke was low-to-moderate, even after many years of research in the field (Mehrholz et al., 2017). Thus, we consider that a combination of treadmill and HAL may not fully utilize the potential of HAL training. Because overground gait training includes a change of direction, we believe that overground gait training with HAL can be performed in a form that is closer to real-life walking.

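### The primary mixed model leaves out age and baseline FAC, the two minimisation factors; if they predict change in FAC, the test is conservative and some power is forgone

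*Protocol article*

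**What the plan says.** Under Allocation and Blinding, the Protocol article describes 1:1 minimisation with "random allocation factors for age (older than 65 years or younger than 65 years) and FAC (scores of 0–1 or ≧2" as its factors. The Discussion gives the purpose: "age and FAC scores will be used as allocation factors to equalize the age and walking ability between the two groups".

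Under Statistical Analysis, the primary outcome variable is change from baseline in FAC at the 4th, 7th and 9th interventions and at 6 months. The sentence on model terms reads "Whereas, group, time point, and the group × time point interaction will be included as the fixed effects". The primary comparison is a t-test on the difference in adjusted means at the end-of-term evaluation, and "The significance level will be 5% on both sides". Secondary continuous outcomes get a similar analysis.

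Under Sample Size, the pilot results are summarised as "the mean difference of the change in the intervention group at the end of the FAC was 0.82 and the combined SD was 0.63". The planning difference was then lowered: "the 50% lower confidence limit of the mean difference, 0.63, was used conservatively". The result is stated as "The minimum sample size necessary for the power of the primary analysis to exceed 0.8 was estimated as 34 in two groups", raised to 40 for missing data.

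**The concern.** Minimisation makes the arms alike on the chosen factors. If those factors predict the outcome, the between-arm difference varies less from one hypothetical trial to the next than under simple randomisation. A model without the factors cannot see this. Their contribution stays in the residual variance, and the reported standard error describes a noisier design than the one used. The confidence interval is then wider than it needs to be and the actual type I error falls below 5%.

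Two further features are relevant. A change score takes baseline into account only with a fixed slope of 1, so any remaining relation between starting level and change goes unmodelled. The minimisation also pools FAC 0 with FAC 1, so variation between those two levels is reduced by neither the design nor the model.

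At stake is the precision of the primary comparison in a trial of 40 patients. The article itself gives some reason to expect age to matter: of an earlier randomised HAL trial it reports that "younger age was determined as the only factor that enhances independent walking".

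**Working it through.** **Inputs from the article.** Two-sided α = 0.05; planning difference 0.63; SD 0.63; 1:1 allocation; 34 evaluable and 40 enrolled; minimisation on age (two bands) and FAC (0–1 versus 2 or more).

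**Inputs assumed, because the article does not give them.** R², the share of the variance of FAC change explained by age and baseline FAC together, from 0 to 0.3 and split equally between the two; minimisation with a biased-coin probability of 0.8; the two age bands, and the three FAC levels 0, 1 and 2, equally frequent; normal errors; complete data; final visit only.

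**Step 1: reproduce the plan's figure.** With n per arm, the noncentrality is 0.63 / (0.63 × √(2/n)) = √(n/2), with 2n − 2 degrees of freedom.
- n = 16: √8 = 2.83, power 0.781.
- n = 17: √8.5 = 2.92, power 0.807. This is the first n above 0.8, so the total is 34, as stated.
- n = 20: √10 = 3.16, power 0.869.
- 34 / 40 = 0.85, an allowance of 15% for missing data.

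The stated sample size is therefore that of an unadjusted two-sample t-test and takes no credit for covariates.

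**Step 2: approximate power with adjustment.** Replace the SD by 0.63 × √(1 − R²) and give up 2 more degrees of freedom. At R² = 0.3 the SD is 0.63 × √0.7 = 0.527.

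| R² | Power, N = 34 | Power, N = 40 |
|---|---|---|
| 0 | 0.805 | 0.868 |
| 0.1 | 0.845 | 0.900 |
| 0.2 | 0.884 | 0.931 |
| 0.3 | 0.921 | 0.957 |

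**Step 3: simulate the allocation.** 20,000 trials per cell, each analysed once with group only and once with group, age band and baseline FAC (0/1/2).

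| N | R² | Type I error, unadjusted | Type I error, adjusted | Model SE / true SE, unadjusted | Power, unadjusted | Power, adjusted | Change in points |
|---|---|---|---|---|---|---|---|
| 34 | 0 | 0.050 | 0.048 | 1.00 | 0.802 | 0.794 | −0.8 |
| 34 | 0.1 | 0.040 | 0.048 | 1.04 | 0.812 | 0.835 | +2.3 |
| 34 | 0.2 | 0.036 | 0.051 | 1.07 | 0.821 | 0.875 | +5.4 |
| 34 | 0.3 | 0.028 | 0.050 | 1.13 | 0.835 | 0.918 | +8.3 |
| 40 | 0 | 0.049 | 0.048 | 1.00 | 0.868 | 0.862 | −0.6 |
| 40 | 0.1 | 0.040 | 0.048 | 1.04 | 0.869 | 0.890 | +2.1 |
| 40 | 0.2 | 0.034 | 0.049 | 1.08 | 0.890 | 0.929 | +3.9 |
| 40 | 0.3 | 0.026 | 0.050 | 1.13 | 0.895 | 0.955 | +6.0 |

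The simulated adjusted power agrees with Step 2 to about one point. A separate single-visit simulation gave slightly larger upper limits, so I quote the wider ranges: about −1 to +7 points at N = 40 and −1 to +9 at N = 34.

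**The case against.** The strongest reply is that nothing in the plan fails. The sample size was computed without covariates, it reproduces, and unadjusted power stays above 0.80 in every cell. The error is on the conservative side. All of this stands. A reader might infer that the trial is underpowered or its primary test invalid; the figures support neither.

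The size of the gain also rests on an R² that the article does not give, and at R² = 0 adjustment costs slightly under one point. The evidence on prognosis is thin. The age finding concerns independent walking in a trial that the Discussion itself contrasts with this one (FAC 0–1, about 5 weeks after onset, treadmill training). Because age was the only factor found there, the finding does not support baseline FAC as a predictor. This stands too, and it is why the range must start at zero.

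Two other readings go too far:
- A reader might infer a ceiling effect from the bounded scale. Entry is restricted to FAC 0–2 on a 0–5 scale, which leaves at least 3 points of room, and no mean change is given. A ceiling effect is therefore not shown.
- A reader might infer that a chance imbalance between FAC 0 and FAC 1 biases the estimate. Such imbalance is part of the random error that the standard error covers. The change score already subtracts the baseline difference itself, and the article lists imbalance outside the allocation factors as a limitation.

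Finally, one might say that covariates belong in the analysis plan, which is not at hand. But the article does not leave the fixed effects open. It names them, and the allocation factors are not among them.

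**Conclusion.** The point holds as a recommended improvement, not as a flaw that invalidates the analysis. The model as stated omits both factors used to allocate patients. If they predict change in FAC, the unadjusted standard error is too large: by about 4% at R² = 0.1 and about 13% at R² = 0.3. The type I error then falls to about 4% and about 3%. If they do not predict it, nothing is lost by the present model.

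The direction follows from the design. The size depends on the assumed R² and on a simplified setting: one visit, no missing data, normal errors. The four-visit model, the discrete FAC score and the baseline-by-time terms were not simulated.

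**What to change.** Before unblinding, state in the protocol or analysis plan that the primary mixed model also includes:
- baseline FAC (0/1/2), taken from the same blinded video review as the outcome;
- age, either continuous or as the minimisation band;
- baseline FAC × time point, if the model can be fitted with it in 40 patients.

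For the secondary continuous outcomes, use each outcome's own baseline value plus age. Report the model without covariates as a sensitivity analysis.

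Both covariates are already needed for allocation, so no new data are required and the sample size need not change. The cost is a few degrees of freedom: slightly under one point of power in the simulated cells if the factors turn out not to be prognostic. The choice should be fixed in advance, because covariates selected after the results are seen would carry little weight.
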